| **Sample Size Considerations** | In performing an observational cohort study, the larger the sample size used for data analysis, the more applicable the results are to the population as a whole. Therefore, COHORT will allow each site to enroll as many subjects as are eligible and willing to participate. Several genetic studies are proposed to delineate the genetic and environmental effects on relevant phenotypic events such as phenoconversion or development of signs of HD. Initial analyses will estimate the proportion of phenotypic variation due to genetic factors and will be followed by studies designed to identify the DNA sequence changes that underlie the phenotypic variation. To estimate the influence of genetic factors, typically samples of 500-1,000 sibling pairs are required to detect genetic contributions of as little as 20%. This would typically be considered the lower bound for a covariate that might be identified, which could act as a meaningful covariate for therapeutic trials aimed at delaying the phenotypic event (e.g., HD phenoconversion). To identify the genes and sequence variation underlying the trait, typically even larger samples are required, but they can include various types of related individuals such as siblings, half siblings, parent-offspring, cousins, etc. A sufficiently large sample size of a relevant phenotypic event (e.g., phenoconversion or development of signs of HD) will provide adequate statistical power to detect a relevant risk factor (e.g., genetic polymorphism or environmental effect) that influences the phenotypic event and that might meaningfully serve as a covariate for therapeutic trials aimed at delaying the phenotypic event (e.g., HD phenoconversion). |

Cooperative Huntington’s Disease Observational Research Trial **(COHORT)**

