# STATISTICAL CONSIDERATIONS

1. **Sample Size Calculation**

Prior to the initiation of studies to identify the genetic determinants of a disease phenotypic, it is essential to first estimate that fraction of the phenotypic variation due to genetic factors. A commonly employed design to perform such an analysis is the collection of sibling pairs with the goal of estimating the heritability of the phenotype of interest. The COHORT sample will recruit multiple members from a family and through the collection of family history information, will be able to establish the biological relationship among individuals and use this information for genetic analyses. Siblings are typically employed for heritability studies since they are closely related and are expected to share, on average, half their genetic material. Studies in COHORT will focus on estimating the heritability of a number of different quantitative phenotypes including the age of onset of disease and the rate of disease progression (as measured by a number of different quantitative traits). In addition, with the collection of a number of novel biomarkers, COHORT is uniquely positioned to estimate the heritability of these biomarkers to determine whether genes are important predictors of their variability. For those phenotypes and traits, which are heritable, the collection of family data as part of COHORT will allow us to initiate studies to identify the genes and polymorphisms contributing to trait variability.

Broad-sense heritability (H2) is estimated as twice the sibling intraclass correlation, according to the method of Falconer (1989).  As shown below, for a phenotypic trait with 50% heritability (i.e. half the phenotypic variation is due to genetic effects), a sample of approximately 100 sibling pairs will have 80% power (with alpha=0.05). As the genetic contribution to the trait decreases, the required sample size increases. For a trait with only 20% heritability, a sample of approximately 600 sibling pairs is required for 80% power.

Falconer DS. 1989. *Introduction to Quantitative Genetics.* 3rd ed. Essex, England: Longman Scientific and Technical.

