The COHORT study was designed to assemble a large descriptive database that will provide the opportunity to study many different factors potentially associated with HD-related events. Some potential factors include history of smoking, current concomitant medication use, or an unknown gene possibly associated with a predisposition to HD. The primary outcome for those affected with HD is progression of disease, which is measured by a decrease in total functional capacity (captured on the UHDRS 99). The primary outcome for those at risk would be phenoconversion or clinical onset of disease.

The table below gives the numbers of events required to detect an increase in risk corresponding to a hazard ratio of the specified magnitude associated with a single risk factor with the specified prevalence. A two-sided alpha level of 5% is assumed. The numbers of events given are for 80% power; for 90% power multiply all entries by 1.34.

| **Risk Factor Prevalence** | **Hazard Ratio** | | | | | | | |
| --- | --- | --- | --- | --- | --- | --- | --- | --- |
| **5.0** | **4.0** | **3.0** | **2.5** | **2.0** | **1.8** | **1.6** | **1.5** |
| **1%** | 306 | 412 | 656 | 943 | --- | --- | --- | --- |
| **2%** | ***154*** | ***208*** | 331 | 476 | 833 | --- | --- | --- |
| **3%** | ***104*** | ***140*** | 223 | 321 | 561 | 780 | --- | --- |
| **4%** | ***79*** | ***106*** | ***169*** | 243 | 425 | 591 | 924 | --- |
| **5%** | ***64*** | ***86*** | ***137*** | ***197*** | 344 | 478 | 747 | --- |
| **6%** | ***54*** | ***72*** | ***115*** | ***166*** | 289 | 402 | 629 | 846 |
| **8%** | ***41*** | ***55*** | ***88*** | ***127*** | 222 | 308 | 482 | 648 |
| **10%** | ***34*** | ***45*** | ***72*** | ***104*** | ***181*** | 252 | 394 | 530 |
| **12%** | ***29*** | ***39*** | ***62*** | ***88*** | ***155*** | ***215*** | 336 | 452 |
| **14%** | ***25*** | ***34*** | ***54*** | ***78*** | ***136*** | ***188*** | 295 | 396 |
| **16%** | ***23*** | ***30*** | ***48*** | ***69*** | ***121*** | ***169*** | 264 | 355 |
| **18%** | ***21*** | ***28*** | ***44*** | ***63*** | ***111*** | ***154*** | 240 | 323 |
| **20%** | ***19*** | ***25*** | ***41*** | ***58*** | ***102*** | ***142*** | 222 | 298 |
| **25%** | ***16*** | ***22*** | ***35*** | ***50*** | ***87*** | ***121*** | ***189*** | 254 |
| **30%** | ***14*** | ***19*** | ***31*** | ***44*** | ***78*** | ***108*** | ***169*** | 227 |

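### Twice the full-sibling correlation is labelled broad-sense heritability, although it counts shared sibling environment twice and dominance only half

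*Protocol*

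**What the plan says.** Section VIII a) (Sample Size Calculation) says that before gene-finding studies begin "it is essential to first estimate that fraction of the phenotypic variation due to genetic factors". The design offered for this is sibling pairs, chosen because siblings are "expected to share, on average, half their genetic material". The estimator follows: "Broad-sense heritability (H2) is estimated as twice the sibling intraclass correlation", with a quantitative-genetics textbook cited as the source. The next sentence shows how the result is to be read: "for a phenotypic trait with 50% heritability (i.e. half the phenotypic variation is due to genetic effects". About 100 pairs are said to give 80% power at that level with alpha 0.05, and then: "For a trait with only 20% heritability, a sample of approximately 600 sibling pairs is required for 80% power".

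The Synopsis (Sample Size Considerations) has the same plan: "Initial analyses will estimate the proportion of phenotypic variation due to genetic factors". It quotes 500 to 1,000 sibling pairs for genetic contributions as small as 20%.

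The text of Section VIII a) sets no condition of zero shared environment or zero dominance, and describes no adjustment for either. Section II (Background and Rationale) says that environmental factors influence age at onset, which is one of the traits that Section VIII a) names for heritability estimation.

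**The concern.** Siblings resemble one another because they share genes and because they usually share an upbringing. A correlation among full siblings cannot tell the two apart, and doubling it doubles both. Dominance works the other way: siblings share only a quarter of it, so doubling recovers half, whereas broad-sense heritability should contain all of it. The quantity named in the protocol is therefore not in general what the estimator returns.

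What is at stake is the interpretation of the initial genetic analyses. A trait that runs in families for environmental reasons could be described as heritable and the result used to motivate a search for genes. A trait with substantial dominance could be understated. More sibling pairs shrink the standard error but leave the bias in place.

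**Working it through.** **Inputs from the protocol** (Section VIII a) and Synopsis): estimator 2t, where t is the sibling intraclass correlation; 100 pairs at 50% heritability (t = 0.25) and 600 pairs at 20% (t = 0.10); 80% power; alpha 0.05; 500 to 1,000 pairs as the Synopsis range.

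**Input assumed:** c2, the shared-environment share of variance, at 0.05 to 0.10. The protocol gives no figure.

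**Step 1. Reproduce the pair counts.** Test t = 0 with Fisher's z: n = ((z_alpha + z_power) / atanh(t))² + 1.5.

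- One-sided 5%: (1.645 + 0.842)² = 6.183. At t = 0.25, atanh(t) = 0.2554 and n = 96.3. At t = 0.10, atanh(t) = 0.1003 and n = 615.6. With +3 in place of +1.5, the results are 97.8 and 617.1. These agree with the approximate 100 and 600.
- Two-sided 5%: (1.960 + 0.842)² = 7.849, giving 121.8 and 781.2 pairs. At 100 and 600 pairs the two-sided power would be about 0.72 and 0.69.

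The stated counts therefore correspond to a one-sided test.

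**Step 2. What 2t measures.** Write VA, VD and c2 for the additive, dominance and shared-environment shares of total variance, without epistasis.

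- Full-sibling correlation: t = VA/2 + VD/4 + c2
- Estimator: 2t = VA + VD/2 + 2·c2
- Broad-sense heritability: H2 = VA + VD
- Difference: 2t − H2 = 2·c2 − VD/2

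The difference is zero only if c2 = VD/4, that is, if both are zero or they happen to cancel. It is positive if c2 > VD/4 and negative if c2 < VD/4.

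**Step 3. Size under assumed values.** The probability of a significant result at n pairs, one-sided 5%, is Φ(atanh(t)·√(n − 1.5) − 1.645).

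| VA | VD | c2 | True H2 | Reported 2t | P(significant), 600 pairs |
|---|---|---|---|---|---|
| 0 | 0 | 0.05 | 0 | 0.10 | 0.34 |
| 0 | 0 | 0.10 | 0 | 0.20 | 0.79 |
| 0.20 | 0 | 0 | 0.20 | 0.20 | 0.79 |
| 0.20 | 0 | 0.05 | 0.20 | 0.30 | 0.98 |
| 0.20 | 0 | 0.10 | 0.20 | 0.40 | 1.00 |
| 0 | 0.20 | 0 | 0.20 | 0.10 | 0.34 |

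For the second row, atanh(0.10)·√598.5 = 2.455, and Φ(2.455 − 1.645) = 0.79. A simulation of 20,000 studies of 600 pairs under that row gave a mean estimate of 0.200 and a rejection rate of 0.79. Over 500 to 1,000 pairs the probability runs from 0.72 to 0.94 at c2 = 0.10, and from 0.30 to 0.48 at c2 = 0.05.

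Rows two and three give the same correlation, so sibling pairs alone cannot distinguish them. The last row shows the opposite error: pure dominance of 20% is reported as 10%.

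**The case against.** The strongest reply is that this is one sentence in a planning paragraph. Section VIII b) leaves the statistical methods to be settled later. Section VIII a) says that biological relationships among family members will be used in genetic analyses, and Section VI (Data Management, Indiana University) plans family-structure files for that purpose. Nothing prevents a pedigree model. That is right as far as it goes, and it makes the repair easy. It does not retract an estimator and a label that the protocol states outright.

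Four stronger readings are tempting, and the document does not support them:

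- *A go/no-go gate that shared environment could pass.* Section VIII a) says only that family data will allow gene-finding studies for heritable traits. It sets no threshold, test or decision rule. CAG and modifier genotyping of adults goes ahead whatever the heritability result.
- *A design sized on a 20% effect.* Section III puts no limit on sample size. The Synopsis offers 20% as a typical lower bound, not a target.
- *Wrong pair counts.* They reproduce for a one-sided test, which is a natural choice when the alternative is a positive heritability. The line "A two-sided alpha level of 5% is assumed" belongs to the hazard-ratio table. Section VIII a) also points to a heritability display that is absent from the text at hand and may have stated the sidedness.
- *A contradiction with the Synopsis on separating genetic from environmental effects.* That aim is attached to several studies, not to the sibling correlation alone.

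It is also fair to say that the 5% to 10% range is hypothetical and that the false-finding case needs zero genetic variance.

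**Conclusion.** The point holds as a mislabelled and generally biased estimator. Twice the full-sibling correlation is VA + VD/2 + 2·c2, not VA + VD, and Section VIII a) reads it as the genetic share without stating the conditions under which that would be true. This rests on the variance algebra alone (full siblings, no epistasis), not on what the cited textbook says.

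The size depends on a quantity that the protocol does not give. Each percentage point of shared environment adds two to the reported heritability, so an assumed 5% to 10% adds 10 to 20 points. If there were no genetic variance, the whole reported figure would be spurious and significant at 600 pairs with probability about 0.34 to 0.79. Each point of dominance takes half a point off the estimate as a measure of H2.

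A reader might infer that 2t is at least a safe upper bound. It bounds narrow-sense heritability (VA) from above, but not H2, because it falls below H2 whenever c2 < VD/4.

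**What to change.** In Section VIII a):

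1. Drop the broad-sense (H2) label. Describe twice the sibling correlation as a measure of familial resemblance that is an upper bound on narrow-sense heritability only.
2. Base the heritability estimate on a pedigree variance-components model over the relative types already enrolled (siblings, parents, children, grandparents and grandchildren), with a separate shared sibling or household term. The family-structure files planned at Indiana University supply the input.
3. As a minor clarification, state that the 100 and 600 pairs are for a one-sided 5% test. If a two-sided test is meant, the counts become about 122 and 781.

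The cost is a few sentences and standard pedigree software. No new data collection is needed. Intervals will be somewhat wider once shared environment is estimated instead of being taken as zero.

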**b) Data Analysis**

Statistical and analytical methods will be determined by the Huntington Study Group (HSG) with guidance from Biostatistics at the University of Rochester and carried out through the Clinical Trials Coordination Center of the Movement Disorders Unit, Department of Neurology, University of Rochester.

    **Appendix**

    *(Includes other associated protocol documents)*

    Family History Questionnaire (revised 8/31/06)

    Family History Update (revised 8/31/06)

    COHORT Data & Specimen Repository Access Policy and Procedures

    [↑](#endnote-ref-53)
